### 2.8. Statistical Methods

All statistical analyses will be conducted using Jamovi (version 2.6.23), an open-source statistical software based on the R 4.5.0 framework. A significant threshold of *p* < 0.05 will be applied to all analyses. Parametric methods will be employed under the assumptions of normality and homogeneity of variance, verified by Shapiro-Wilk or Kolmogorov-Smirnov and Levene’s tests, respectively. Non-parametric tests will be used if assumptions are violated.

#### 2.8.1. Experiment 1

A 2 × 2 × 3 mixed-design ANOVA will be conducted to analyze differences in MEP amplitudes, with group (Vax vs. No-Vax) as a between-subjects factor, muscle (deltoid vs. extensor carpi radialis), condition (Blood, COVID-19, influenza), as within-subjects factors.

EMG activity from the levator labii superioris (disgust) and corrugator supercilii (fear) will be analyzed using a 2 × 2 × 3 mixed-design ANOVA, incorporating group (Vax vs. No-Vax), muscles (levator labii superioris, corrugator supercilii), condition (Blood, COVID-19, influenza).

Significant interactions (*p* < 0.05) will be followed by Tukey’s HSD post hoc tests to identify condition-specific effects.

#### 2.8.2. Experiment 2

Habituation, fear acquisition, extinction, and recall will be assessed through Skin Conductance Response (SCR) amplitudes using a 2 × 2 × 3 mixed-design ANOVA. The analysis will compare responses to stimuli (CS+ threat-associated stimulus, CS− safety-associated stimulus) as a within-subjects factor, across groups (Vax vs. No-Vax) as a between-subjects factor and phases (habituation, fear acquisition, fear extinction) as a within-subjects factor. Similarly, subjective fear/disgust ratings (Likert scale) will be analyzed using a 2 × 2 × 3 mixed-design ANOVA, with group (Vax vs. No-Vax) as a between-subjects factor, and stimulus Type (CS+ vs. CS−) and phase (habituation, fear acquisition, fear extinction) as within-subjects factors. Significant interactions (*p* < 0.05) will be followed by Tukey’s HSD post hoc tests to identify condition-specific effects.

Pearson’s or Spearman’s correlations (depending on normality) will examine associations between psychometric measures (i.e., disgust sensitivity, anxiety) and neurophysiological markers (MEPs, SCR, EMG). To address inflated Type I error rates due to multiple comparisons, all correlation analyses will be corrected using Bonferroni correction. This method adjusts the family-wise error rate by dividing the overall significance threshold (α = 0.05) by the number of comparisons performed. Hierarchical regression models will assess whether psychological variables are associated with physiological responses. Associations with VH will be explored through between-group comparisons.

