## 3. Discussion

This study aims to provide novel insights into the psychophysiological correlates of vaccine hesitancy (VH). Grounded in the Somatic Marker Hypothesis [25], we hypothesize that bodily and emotional responses will play a crucial role in shaping vaccination attitudes. By investigating sensorimotor mapping, affective learning processes, and psychological predictors of VH, we seek to contribute to a more comprehensive understanding of this phenomenon.

### 3.1. Experiment 1

We predict significant differences in motor evoked potentials (MEPs) between vaccine-hesitant and vaccine-accepting individuals when exposed to COVID-19 vaccination imagery. Specifically, hesitant individuals may exhibit reduced MEP amplitudes in the deltoid muscle—a key muscle involved in vaccine administration—suggesting altered sensorimotor resonance in response to vaccination stimuli. This would align with previous research on embodiment, which posits that motor responses are modulated by observed actions [48,49]. The sensorimotor resonance may serve as a proxy for embodied affective states such as disgust or fear—emotions that are central to the Somatic Marker Hypothesis, which emphasizes the role of visceral and emotional signals in guiding behavior and cognition [25]. Therefore, a decrease in MEP amplitude may indicate a disruption of somatic marker signals, given that corticospinal excitability is sensitive to modulation by negative emotional states. This interpretation is supported by prior work demonstrating the influence of emotions—particularly aversive or defensive states on motor system activity [39,40,41,50,51,52,53]. We suggest that motor resonance changes, in this context, may index the embodied affective experience central to the SMH, thereby linking motor excitability to emotional and interoceptive processing.

Additionally, we anticipate increased facial electromyography (EMG) activity in the levator labii superioris and corrugator supercilii muscles in vaccine-hesitant individuals, reflecting higher levels of disgust and fear responses. If confirmed, these results would support the hypothesis that VH is influenced by affective biases linked to disgust sensitivity and anxiety [9,21].

### 3.2. Experiment 2

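### If the assumption pre-tests fail, the main factorial analyses switch to unnamed non-parametric tests, and the usual rank tests cannot test the interactions the hypotheses need

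*Protocol article*

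**What the plan says.** The opening paragraph of section 2.8 (Statistical Methods) applies to both experiments. It says "Parametric methods will be employed under the assumptions of normality and homogeneity of variance", to be "verified by Shapiro-Wilk or Kolmogorov-Smirnov and Levene’s tests, respectively", and then "Non-parametric tests will be used if assumptions are violated". The same paragraph says "A significant threshold of *p* < 0.05 will be applied to all analyses".

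The main analyses follow. For Experiment 1 (2.8.1): "A 2 × 2 × 3 mixed-design ANOVA will be conducted to analyze differences in MEP amplitudes", with group, muscle and condition as factors. For Experiment 2 (2.8.2), the phases are assessed through "Skin Conductance Response (SCR) amplitudes using a 2 × 2 × 3 mixed-design ANOVA", with group, stimulus and phase as factors. In both, significant interactions "will be followed by Tukey’s HSD post hoc tests to identify condition-specific effects".

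The Discussion (3.1) expects that, for COVID-19 vaccination images, "hesitant individuals may exhibit reduced MEP amplitudes in the deltoid muscle". Section 3.2 expects larger responses to CS+ during acquisition and weaker extinction in the hesitant group. The sample-size sections (2.1.2 and 2.2.2) both target the mixed ANOVA.

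Section 2.6.1 log-transforms the MEPs. The article states no transformation for facial EMG (2.6.1) or SCR (2.6.2).

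**The concern.** The fallback rule and the design do not fit together. The main MEP prediction concerns one muscle and one type of image, and the main SCR prediction concerns one stimulus in particular phases. Both are statements about how a group difference varies across within-participant conditions, so they are interactions.

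The tests most readers would understand by the fallback sentence compare groups on one score, or conditions within one sample. Applied to the outcomes as recorded, they have no term for a group difference that varies by muscle and condition, or by stimulus and phase. If the switch occurs and such tests are used, the planned interaction test and its Tukey follow-up have no counterpart, and the stated power no longer refers to the analysis performed.

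The rule also leaves the choice of main analysis to pre-test results. Shapiro-Wilk and Kolmogorov-Smirnov are joined by an unresolved choice, and at 20 per cell they differ greatly in how often they reject.

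**Working it through.** **Inputs.** Two groups of 20 (2.1.1, 2.2.1). Six repeated measures and r = 0.5 (2.1.2, 2.2.2). Hence 2 × 6 = 12 cells of 20. Applying the 0.05 threshold to each pre-test, and counting any one failure as a violation, are assumptions. The article states no trigger rate, so there is no figure of its own to reproduce. Its sample size enters only as the cell size.

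**What would be lost.** In a 2 × 2 × 3 mixed ANOVA with 40 participants, the three-way interaction has (2−1)(2−1)(3−1) = 2 numerator and (40−2) × 2 = 76 denominator degrees of freedom. Mann-Whitney and Kruskal-Wallis compare groups on one score. Wilcoxon and Friedman compare conditions within one sample. None contains this term.

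**Closed-form check of the trigger rate.** For independent tests on exactly normal data:
- 12 Shapiro-Wilk tests: 1 − 0.95^12 = 0.46.
- The same plus six Levene tests, one per measure: 1 − 0.95^18 = 0.60.

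**Simulation.** Correlated data at r = 0.5, 1,500 to 3,000 data sets per setting for the normal case. The skewed case is an assumption: log-normal, with r = 0.5 on the log scale. Its skewness is (e^(σ²) + 2)√(e^(σ²) − 1), which is 0.78 at σ = 0.25 and 1.75 at σ = 0.5. Where repeated runs differed, the range is shown.

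| Reading of the rule (any p < 0.05 triggers) | Exactly normal | σ = 0.25 | σ = 0.5 |
|---|---|---|---|
| Shapiro-Wilk in each of 12 cells | 44–45% | 89–90% | 100% |
| Same, plus six Levene tests | 60% | 93% | 100% |
| One Shapiro-Wilk on residuals from cell means | 10% | 93–94% | 100% |
| Same, plus six Levene tests | 34–35% | 96% | 100% |
| One Shapiro-Wilk on residuals with participant means also removed | 5% | 51–56% | 98–99% |
| Uncorrected Kolmogorov-Smirnov in each of 12 cells | about 0% | 1% | 16–17% |
| Same, plus six Levene tests | 27–28% | 33% | 54% |

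**Dependence on r (normal data).** Per-cell Shapiro-Wilk plus Levene triggers in 62% at r = 0, 57% at r = 0.7 and 45% at r = 0.9.

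**Reading the table.** With normal data the switch is rare or frequent depending on details the rule does not fix. With skewed data every Shapiro-Wilk reading triggers in at least half of studies at σ = 0.25 and nearly always at σ = 0.5. Kolmogorov-Smirnov alone mostly does not. The choice between the two normality tests can therefore decide which main analysis is run.

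**The case against.** The strongest defence is that the sentence names no replacement test. Permutation tests and the aligned-rank-transform ANOVA are non-parametric and keep the interaction, and a Mann-Whitney test on a within-participant difference score tests a single interaction contrast. Much of the remaining detail (unit of checking, number of failures) could stand in a fuller document. This stands in part. A reader might infer that the rule, followed literally, discards the interaction test. The text does not say so: that happens only if the customary one-factor tests are applied to the recorded outcomes. But the switch itself is stated, it covers the main analyses, and nothing restricts it to methods that suit them.

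Other stronger readings also fail:

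- **That the switch occurs about half the time with perfect data.** This holds for per-cell Shapiro-Wilk with any failure counting. The article does not fix that reading, and others give about 0% to 35%.
- **That every hypothesis is an interaction.** Section 3.1 expects higher activity in both facial muscles in hesitant participants, which is a group difference. The trait hypotheses rest on group comparisons and correlations, for which classical rank methods are suitable.
- **That rank tests would themselves create false condition-specific findings.** With a uniform group effect of d = 0.5, cell-by-cell Mann-Whitney tests give a mixed significant and non-significant pattern in about 66% to 68% of simulated studies, but t-tests do so in about 66% to 67%. This reflects low power per cell, and the article plans no such inference.
- **That SCR is bound to fail the pre-tests.** The documents give no SCR distribution, so the skewed columns are assumptions. A σ of 0.5 is substantial skew, not mild. The MEPs are already log-transformed.

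**Conclusion.** The point holds in a limited form. The plan makes the main mixed ANOVAs give way to unnamed non-parametric tests when pre-tests fail. With the usual one-factor rank tests, the interactions behind the main MEP and SCR hypotheses would go untested, and the power calculations would not apply.

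The size depends on the reading. For exactly normal data the switch occurs in about 0% to 60% of studies. Under the assumed log-normal skew, Shapiro-Wilk per cell or on residuals from cell means triggers it in about 90% to 100%. On residuals with participant means removed, the rate is about 51% to 99%. These figures assume 20 per group, r = 0.5, a 0.05 level for each pre-test and any single failure counting. This should be changed before data are seen. It does not invalidate the design.

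**What to change.** Restrict the rule, for the factorial analyses only:

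- Keep the mixed model as the primary analysis whatever the pre-tests show.
- Log- or square-root-transform SCR and facial EMG, in line with the existing log transformation of MEPs.
- Check the model residuals, not the raw cells, and say which residuals.
- If they remain clearly non-normal, report one named interaction-preserving sensitivity analysis beside the primary result, such as a participant-level permutation or bootstrap of the mixed model, or an aligned-rank-transform ANOVA.

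The non-parametric rule can stay for two-group questionnaire comparisons and for correlations, where section 2.8 already provides for Spearman.

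The cost is a paragraph of wording and a few lines of R beyond the Jamovi menus. It needs no extra participants or measurements.

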## Abstract

**Background:** Vaccine hesitancy (VH) is a significant public health challenge, especially during the COVID-19 pandemic. Despite extensive research on the psychological and socio-political determinants of VH, its psychophysiological mechanisms remain unexplored. Grounded in the Somatic Marker Hypothesis, this study aims to investigate the neurophysiological and affective processes underlying VH. **Methods:** Two experiments will assess sensorimotor resonance and affective processes in VH. In the first experiment, motor-evoked potentials (MEPs) will be recorded from the deltoid and extensor carpi radialis muscles while participants view images of people receiving COVID-19 and influenza vaccines, as well as blood injections (Block 1), and images of vial containing the same substances (Block 2). Facial electromyographic (EMG) activity will measure disgust and fear responses. In the second experiment, skin conductance response (SCR) will be recorded during a virtual reality-based fear conditioning and extinction paradigm. **Expected Outcomes:** We hypothesize that vaccine-hesitant individuals will exhibit altered sensorimotor resonance, higher affective responses to vaccination stimuli, and impaired fear extinction learning. Psychological traits such as disgust sensitivity, paranoia, anxiety, and dogmatism are expected to be associated with VH. **Conclusions:** By identifying the psychophysiological mechanisms of VH, this study will contribute to developing effective vaccine promotion strategies to address future public health emergencies.

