#### 2.1.2. Sample Size Calculation

The required sample size was determined a priori using GPower 3.1 [28], targeting the primary statistical analysis: a mixed-model ANOVA with 2 between-subjects groups (Vax vs. No-Vax) and 2 within-subjects factors—muscle (deltoid vs. extensor carpi radialis) and condition (Blood, COVID-19, Influenza). The analysis aimed to detect a medium effect size (f = 0.25), considered the smallest scientifically meaningful effect size [29], with a power of 0.95 and α = 0.05. Given the repeated-measures structure, the analysis assumed a moderate correlation (r = 0.5) between the six repeated measurements (2 muscles × 3 conditions), which reflects the expected level of association in related psychometric constructs such as disgust sensitivity and anxiety. This correlation value was specified in GPower to ensure accurate estimation. Under these parameters and assuming ideal sphericity (ε = 1), the required sample size was estimated at 40 participants.

### 2.2. Experiment 2

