### 2.7. Interventions

#### 2.7.1. Experiment 1

Prior to the experimental session, participants will complete demographic and psychological questionnaires. Following screening, the optimal scalp positions (OSP) and resting motor threshold (rMT) for the target (deltoid) and control (extensor carpi radialis) muscles will be determined. Participants will be seated 80 cm from a computer screen in a dimly lit room. The experimental visual stimuli will consist of pictures depicting scenes of vials and ongoing injections referring to blood sampling, COVID-19 vaccine, and influenza vaccine subtending a 10.5 × 5.8 cm region plus a neutral control stimulus consisting of a scrambled picture of the same dimension and form (see Figure 2).

For each type of stimulus in both blocks, 20 MEPs will be recorded. To ensure a balanced and unbiased presentation, stimuli will be randomly presented. A total of 16 MEPs per muscle and condition will be obtained and stored for offline analysis.

During stimulus presentation, TMS pulses will be delivered at 120% of rMT at randomized intervals (1100–1400 ms post-stimulus onset) to mitigate priming effects. EMG will record muscle activity from the levator labii superioris, which is associated with disgust responses, and the corrugator supercilii, linked to fear responses. Additionally, following the TMS session, participants will be presented again with the same set of pictures and will ask to rate their emotional responses using a 7-point Likert scale, where 1 indicated no emotional reaction and 7 indicated a very strong emotional reaction. Specifically, they were asked to evaluate the extent to which each image elicited feelings of alarm, disgust, fear, and anger.

#### 2.7.2. Experiment 2

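### Experiment 1 manipulates block (injection scenes versus vials), but block is in neither planned ANOVA nor the power calculation, so no planned test covers the injection-versus-vial contrast between groups

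*Protocol article*

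**What the plan says.** The Abstract sets out two numbered blocks. The first shows people receiving the two vaccines, "as well as blood injections (Block 1), and images of vial containing the same substances (Block 2").

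Section 2.7.1 confirms both kinds of picture, "pictures depicting scenes of vials and ongoing injections referring to blood sampling, COVID-19 vaccine, and influenza vaccine", "plus a neutral control stimulus consisting of a scrambled picture of the same dimension and form". On recording it says: "For each type of stimulus in both blocks, 20 MEPs will be recorded". Shortly afterwards it says: "A total of 16 MEPs per muscle and condition will be obtained and stored for offline analysis".

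Section 2.8.1 fixes the MEP analysis as a 2 × 2 × 3 mixed ANOVA with group between subjects and "muscle (deltoid vs. extensor carpi radialis), condition (Blood, COVID-19, influenza), as within-subjects factors". The facial EMG analysis has the same form, "incorporating group (Vax vs. No-Vax), muscles (levator labii superioris, corrugator supercilii), condition (Blood, COVID-19, influenza").

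Section 2.1.2 powers "a mixed-model ANOVA with 2 between-subjects groups (Vax vs. No-Vax) and 2 within-subjects factors", the within-subjects factors being muscle and condition. It counts six repeated measurements, and it calls this the primary analysis. No section says that block is a factor, that the ANOVA is run separately by block, or that one block is left out.

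**The concern.** Section 3.1 predicts reduced deltoid MEPs in hesitant participants and reads this as altered sensorimotor resonance, on the ground that observing an action modulates the observer's motor responses. A vial shows a substance and no injection being given. Comparing injection with vial, with the substance held constant, is therefore the contrast in this design that separates a response to an observed injection from a reaction to vaccine content. Section 3.1 itself says that negative emotional states alter corticospinal excitability, so the rival explanation is a real one.

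Without block in the model, a group difference that appears equally for vials and for injections cannot be told apart from one that needs an observed injection. If the blocks are averaged, an effect confined to injection scenes is also diluted. Because the article does not say how block is handled, the choice between pooling and separate analyses stays open until the data are seen.

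**Working it through.** **Cells recorded against cells modelled.** The design gives 2 muscles × 3 substances × 2 blocks = 12 MEP cells per participant, before the scrambled picture. The models and the power calculation use 2 × 3 = 6.

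**What each reading leaves untested.**
- One ANOVA on all the data: each condition mean combines injection and vial trials, and there is no block term.
- One ANOVA per block: each is 2 × 2 × 3, so this also fits section 2.8.1. There is still no test of group × block, and a significant result in one block beside a non-significant result in the other does not show that the blocks differ.

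**The plan's own figure.** Inputs from section 2.1.2: f = 0.25, α = 0.05, power 0.95, k = 2 groups, m = 6, r = 0.5, ε = 1, N = 40. For the within-between interaction in the usual repeated-measures form:

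λ = f²·N·m/(1 − r), df1 = (k − 1)(m − 1), df2 = (N − k)(m − 1).

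At N = 40, λ = 0.0625 × 40 × 6/0.5 = 30, with df 5 and 190, and power is 0.9945. The smallest N reaching 0.95 is 28 (power 0.954), so the stated inputs do not return 40. Entering four groups instead of two does return 40 (power 0.952). That mismatch is a separate matter, and the present point does not depend on it.

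**Cost of pooling, if it happens.** Assumptions: the group effect (f = 0.25) exists only in the injection block, the two blocks are averaged with equal weight, and r = 0.5 still holds among the six pooled means. Averaging halves the effect and multiplies the error SD by √((1 + r_b)/2), where r_b is the between-block correlation:

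f_pooled = 0.25 × 0.5/√((1 + r_b)/2).

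The article gives no r_b, so the full range from 0 to 1 is shown.

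| r_b | f_pooled | λ at N = 40 | Power at N = 40 (df 5, 190) | N for 95% power |
|---|---|---|---|---|
| no dilution | 0.250 | 30 | 0.99 | 28 |
| 0 | 0.177 | 15 | 0.86 | 54 |
| 0.5 | 0.144 | 10 | 0.66 | 82 |
| 1 | 0.125 | 7.5 | 0.52 | 108 |

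If the same λ is assigned to the group × muscle × condition term alone (df 2 and 76), power goes from 0.999 to 0.94, 0.80 and 0.67. The loss is smaller, but the direction is the same.

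**After adding block.** With m = 12 and the other inputs unchanged, λ = 0.0625 × 40 × 12/0.5 = 60, with df 11 and 418. Power is above 0.999, and N = 18 reaches 0.95. This keeps f = 0.25 and r = 0.5 across 12 measurements, and it is not a calculation for the four-way term itself.

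**The case against.** Several counter-arguments have force.

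- **Pooling is not documented.** A reader might infer that the plan averages injection and vial trials. It does not say so, and an ANOVA run once per block fits the text. The count of 16 MEPs per muscle and condition may even suit a within-block cell better, since merging the blocks could give up to 40 per condition. This stands. The power losses above therefore apply only if the blocks are pooled, but the missing group × block test does not depend on that.
- **The vial is not called a control.** A reader might infer that the plan merges resonance with its designated control. The article's named controls are the scrambled picture and the extensor carpi radialis muscle. The vial serves as a comparator by its place in the design, not by label.
- **The muscle factor already gives specificity.** In part it does: a reaction that shifts both muscles equally would not produce group × muscle × condition. But that tests specificity to the deltoid, and does not show that the effect depends on seeing an injection.
- **The argument does not carry over to facial EMG.** Levator and corrugator activity are recorded as indices of disgust and fear, so the body-specificity reasoning does not apply to them directly. Block belongs in that model for a simpler reason: to avoid merging two kinds of picture without saying so.
- **More terms mean more tests.** A four-factor ANOVA has 15 effects instead of 7. If all were tested independently at 0.05, the chance of at least one false positive would rise from 1 − 0.95^7 = 30% to 1 − 0.95^15 = 54%. This is a fair reason to name the key tests in advance.

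A reader might also infer a fixed block order from the labels 1 and 2, or an outright contradiction between 20 and 16 MEPs. Neither is established. Numbered labels do not fix an order, and 16 may be what remains of 20 after trials are removed.

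**Conclusion.** The point holds in this form: block is manipulated in Experiment 1, the stated models and the power calculation leave it out, and under either reading of section 2.8.1 the group difference between injection and vial responses is not tested. This is not detail that an article leaves out for brevity. The factors and levels are listed in full in section 2.1.2 and twice in section 2.8.1, and they fix a complete model without one manipulated factor.

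The consequence for inference is certain: as planned, the analysis cannot tie a deltoid MEP difference to the sight of an injection. The consequence for power is conditional. It arises only if the blocks are pooled and the effect is confined to injection scenes, and its size depends on a correlation that the article does not state. The MEP counts are a secondary matter of clarity.

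**What to change.** 1. In section 2.8.1, add block (injection versus vial) as a within-subject factor to the MEP ANOVA, making it 2 × 2 × 2 × 3. Do the same for the facial EMG ANOVA so that the two picture types are not merged.
2. Pre-specify group × muscle × condition in the injection block as the primary MEP test, and its interaction with block as the specificity test.
3. In section 2.1.2, change the number of repeated measurements to match the model, and state which term is powered.
4. In section 2.7.1, reconcile the 20 and 16 MEP counts, and say whether 16 is per block.

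The cost is a change of wording. No new data are needed, and by the protocol's own power convention no more participants. The downside is more model terms, which naming the primary and specificity tests in advance contains.

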Through the Pavlovian fear conditioning and extinction paradigm, we expect vaccine-hesitant individuals to exhibit higher skin conductance responses (SCR) to the conditioned stimulus (CS+), indicating exaggerated fear responses during the acquisition phase. Furthermore, we anticipate a lower extinction learning, leading to increased fear retention during the recall session. Such findings would suggest that vaccine-hesitant individuals exhibit altered patterns of threat updating, which could be associated with the persistence of avoidance-related behaviors. These results would align VH with other avoidance-based behaviors, emphasizing the need for interventions targeting fear extinction [22,54]. Consistent with previous research, we anticipate that specific psychological traits will be significantly associated with higher levels of VH. Higher scores in disgust sensitivity, paranoia, and dogmatic thinking are expected to be associated with increased VH. These findings would further emphasize the complex interplay between cognitive rigidity, emotional processing, and vaccine decision-making [19,20,55].

In conclusion, this protocol will have significant public health implications by advancing our understanding of the psychophysiological mechanisms underlying VH. It will offer valuable insights for future pandemics and help develop tailored public health messages that integrate sociocultural, clinical, and neurobiological factors.

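### Tukey's HSD after a significant interaction is the only stated route to the directional predictions; a planned contrast would test them directly and with more power

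*Protocol article*

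**What the plan says.** Section 2.8.1 sets the Experiment 1 analysis: "A 2 × 2 × 3 mixed-design ANOVA will be conducted to analyze differences in MEP amplitudes", with group between subjects and muscle and condition within subjects. The facial EMG analysis, and the skin conductance and rating analyses in section 2.8.2, have the same 2 × 2 × 3 shape. In both experiments the next step is the same: "Significant interactions (*p* < 0.05) will be followed by Tukey"'s "HSD post hoc tests to identify condition-specific effects". The text does not say which cells or pairs form the Tukey family, and it lists no planned contrast.

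The predictions are narrower than this. For COVID-19 vaccination imagery, section 3.1 says "hesitant individuals may exhibit reduced MEP amplitudes in the deltoid muscle". For acquisition, section 3.2 says "we expect vaccine-hesitant individuals to exhibit higher skin conductance responses (SCR) to the conditioned stimulus (CS" (that is, CS+). It then adds weaker extinction learning and more retained fear at recall.

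**The concern.** The follow-up step is where each prediction is confirmed or not, and Tukey on all cells suits it poorly in two ways.

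First, it charges for comparisons nobody wants, such as Vax deltoid Blood against No-Vax extensor influenza. The one comparison that matters must clear a much higher bar.

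Second, it compares cell means, whereas a condition-specific effect is a difference of differences. A Vax/No-Vax gap in the deltoid/COVID-19 cell does not by itself show that the COVID-19 images, and not a wider group difference, produced it. Likewise, a group gap in CS+ responding does not show differential conditioning unless CS− is subtracted.

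The study could therefore report a significant interaction and still be unable to say that it lies where it was predicted.

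**Working it through.** **Inputs from the article.** 20 per group (section 2.1.1). From section 2.1.2: "The analysis aimed to detect a medium effect size (f = 0.25"), "with a power of 0.95 and α = 0.05", and "the analysis assumed a moderate correlation (r = 0.5) between the six repeated measurements", with sphericity assumed. Tests are taken as two-sided; the article does not say.

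**The plan's own figure.** Section 2.1.2 gives N = 40. For the within-between interaction with m = 6 measures, λ = N·m·f²/(1 − r). With two groups, N = 28 already gives 95% power and N = 40 gives 99.5%. N = 40 at 95% appears only if the number of groups is entered as 4. This is a separate matter. It does not affect the calculations below, which take 20 per group as given.

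**Size of the family.** The three-way term has 2 × 2 × 3 = 12 cells and 12 × 11/2 = 66 pairs. Critical |t| = q(0.95; 12, 38)/√2 = 3.48, a nominal p of 0.0013. One planned two-sided test needs t(0.975; 38) = 2.02. The two-way terms are milder: 6 cells (15 pairs) need 3.00, and 4 cells (6 pairs) need 2.69.

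**Effect size (assumption).** The article gives no cell-level effect, so a range is shown. The low end, d = 0.5, is what f = 0.25 means for a two-group main effect. For the high end, place d in one of the 12 cells. Over six levels the interaction variance is then (d²/4) × [(5/6)² + 5 × (1/6)²]/6 = 5d²/144. Setting this equal to 0.25² gives d = 0.25/√(5/144) = 1.34.

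**Planned contrast.** Take the group difference in deltoid COVID-19 minus the mean of deltoid Blood and influenza. With unit variances and r = 0.5, its within-person variance is (1 − 0.5)(1 + ¼ + ¼) = 0.75. The non-centrality is d·√(20/2)/√0.75, which at d = 0.8 is 0.8 × 3.162/0.866 = 2.92. Non-central t with 38 df then gives 81%.

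**Full rule and Holm list.** These were simulated with at least 20,000 trials per setting and the effect only in deltoid/COVID-19. The full rule is a three-way F(2, 76) with p < 0.05, then the 12-cell Tukey test of the group difference in that cell. The Holm list has four contrasts: the group difference in COVID-19 minus Blood and in influenza minus Blood, in each muscle. Its power is for deltoid COVID-19 minus Blood.

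| Cell effect (SD) | F, then Tukey | Holm list of four | One planned contrast |
|---|---|---|---|
| 0.5 | 2% | 16% | 43% |
| 0.8 | 12% | 47% | 81% |
| 1.0 | 29% | 70% | 94% |
| 1.34 | 69% | 94% | >99% |

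**Where the loss arises, at 0.8 SD.** The three-way F has 43% power. Tukey without the F requirement has about 20%. The F test followed by an unadjusted cell test reaches about 35%. Adding Tukey brings it down to 12%. Among trials with a significant F, 29% pass Tukey in the predicted cell, so 71% detect an interaction without showing it there.

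**A uniform group shift.** With 0.8 SD added in all cells of one group and no interaction, F then Tukey flags the deltoid/COVID-19 cell in about 1.3% of trials.

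**The case against.** Tukey's HSD after a significant interaction is conventional and conservative, and nothing in section 2.8 contradicts itself. Several stronger conclusions that a reader might draw are not supported.

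- *That the plan commits to 66 comparisons.* It does not. The text states no family, and group comparisons within each condition would also fit its wording. Twelve cells is the ordinary reading of Tukey on a three-way term; two-way terms have 4 or 6.
- *That the interaction goes untested, or that a general group difference would pass as condition-specific.* The F test does test the interaction, and the 1.3% figure shows that the F requirement largely blocks the uniform-shift scenario. What stands is narrower: cell pairs do not localise what F has found.
- *That the plan has 12% power where 80% was available.* This holds at one assumed effect against one unadjusted contrast. The full rule runs from 2% to 69% over the range shown, and a four-contrast Holm list reaches 47%, not 81%, at 0.8 SD.
- *That Tukey alone causes the loss.* Part of it comes from the F requirement.
- *That the figures apply to every outcome.* The one-cell scenario fits the motor evoked potential prediction only. The article predicts higher activity in both facial muscles and several differences in Experiment 2.

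It is fair to add that a condensed article may leave the exact family to a fuller plan. But the choice of Tukey after a significant interaction is stated, and it is the only confirmatory route shown.

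**Conclusion.** The concern holds as a question of matching the analysis to the hypotheses; it is not an error in the article. The predictions are specific and directional, and the stated follow-up is an all-pairs procedure reached only through a significant F. Under the stated sample size and correlation, with the effect confined to the predicted cell, the planned contrast has more power at every effect size tried: 43% against 2% at 0.5 SD, 81% against 12% at 0.8 SD, and over 99% against 69% at 1.34 SD.

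These figures rest on an assumed cell effect, equal variances, compound symmetry at r = 0.5 and a 12-cell Tukey family. A narrower family would reduce the loss. The point that cell pairs do not localise the interaction does not depend on the effect size, and it carries over to facial EMG and Experiment 2, where the power figures do not.

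**What to change.** Add a paragraph to section 2.8 naming the planned contrasts, to be tested whether or not the omnibus F is significant.

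- *Experiment 1, motor evoked potentials:* one primary contrast, the group difference in deltoid COVID-19 minus the mean of deltoid Blood and influenza. Report the same contrast in the extensor carpi radialis as a specificity check.
- *Experiment 2, skin conductance:* the group difference in CS+ minus CS− at acquisition and at extinction, plus the recall comparison that section 3.2 predicts, Holm-adjusted within this list. Define the recall comparison on the stimuli actually shown; section 2.7.2 mentions only CS+ there.
- *Everything else:* keep the ANOVAs, and report Tukey comparisons of other cell pairs as descriptive.

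The cost is analysis wording only: no participants, no extra data, and estimated marginal means in the stated software suffice. The change must be made before the data are seen. The main downside is that unplanned cell pairs lose confirmatory status. The Experiment 1 contrast is also aimed at a COVID-19-specific effect. If influenza images produced the same group difference d, its expected value would fall to d − (0 + d)/2 = d/2, so the choice of comparator should be justified in the text.
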